## Abstract

**Background:**

The rehabilitation of paretic stroke patients uses a wide range of intervention programs to improve the function of impaired upper limb. A new rehabilitative approach, called action observation therapy (AOT) is based on the discovery of mirror neurons and has been used to improve the motor functions of adult stroke patients and children with cerebral palsy. Recently, virtual reality (VR) has provided the potential to increase the frequency and effectiveness of rehabilitation treatment by offering challenging and motivating tasks.

**Methods:**

The purpose of the present project is to design a randomized controlled six-month follow-up trial (RCT) to evaluate whether action observation (AO) added to standard VR (AO + VR) is effective in improving upper limb function in patients with stroke, compared with a control treatment consisting of observation of naturalistic scenes (CO) without any action content, followed by VR training (CO + VR).

**Discussion:**

AO + VR treatment may provide an addition to the rehabilitative interventions currently available for recovery after stroke and could be utilized within standard sensorimotor training or in individualized tele-rehabilitation.

**Trial registration:**

The trial has been prospectively registered on ClinicalTrials.gov. NCT05163210. 17 December 2021.

**Supplementary Information:**

The online version contains supplementary material available at 10.1186/s12883-022-02640-2.

## Background

Stroke is the leading cause of disability among adults, and more than 60% of stroke survivors have motor deficits, particularly those related to the upper limb [1]. Stroke rehabilitation usually involves intensive motor training to promote adaptive plasticity by reducing motor deficits and developing new motor learning strategies [2, 3]. It has recently been proposed that the systematic use of action observation (AO) followed by imitation (known as action observation therapy [AOT]) is an effective way to improve motor function and to promote upper limb recovery in patients with motor disorders [4–7]. During a typical AOT session, a series of daily life actions (e.g., grasping a key and inserting it into a lock) are practiced for two to five weeks, with a frequency of three to five sessions per week. During each rehabilitation session, the patient is instructed by the therapist to observe a specific action performed by an actor, presented in a short video-clip on a monitor, and afterwards to reproduce the previously observed action with the paretic limb. The videos usually present a single motor act observed from different perspectives (e.g., subjective, front, or side view). This therapy is based on the neural model of the mirror neuron system (MNS), originally discovered in the monkey premotor and parietal cortex, which is formed by visuomotor neurons that become active both when a monkey performs a goal-directed motor act and when it simply observes the same or a similar motor act performed by the experimenter [8, 9]. A comparable MNS has been identified in humans using different electrophysiological and neuroimaging techniques [10]. In humans, the two main nodes of the MNS are the inferior parietal lobule (IPL) and the ventral premotor cortex (PMv), plus the caudal part of the inferior frontal gyrus (IFG) [11, 12]. 

In the first clinical trial focusing on, Ertelt and colleagues [13] found a significant improvement, evaluated by clinical functional scales, in adult patients with moderate upper limb motor deficits following the application of 18 sessions of AOT, corroborated by a significant increase in activation of the cortical MNS. This improvement was maintained for at least eight weeks after the conclusion of the treatment. More recently, Franceschini and colleagues [14, 15] performed two randomized controlled observer-blinded trials (RCTs) to evaluate the effectiveness of AOT as an add-on treatment to standard upper-limb rehabilitation in acute stroke patients, in which several measures of motor impairment and functional ability demonstrated an improvement over time. The efficacy of AOT has been confirmed in patients with Parkinson’s disease [16, 17], unilateral cerebral palsy (UCP) [18–22] and post-surgical orthopedic patients [23]. AOT is considered particularly useful for activating the motor system in conditions in which intensive motor training is not feasible because of the severity of the impairment of motor function or due to the presence of pain, inflammation, or muscle fatigue [7].

In recent years, new virtual reality-based (VR) rehabilitation treatments have been introduced in order to present rehabilitation exercises in a more practical and friendly setting [24]. These treatments are generally well accepted by patients because they offer several advantages: relatively low cost (in particular for semi-immersive versions), an engaging environment, the real-time personalization of exercises, greater adaptability to the patient’s clinical features and progress, and the opportunity for patients to record their motor performance and get feedback in real time. Furthermore, VR exercises usually require minimal supervision from a therapist, thereby facilitating home-based rehabilitation [25].

Several studies support the application of VR methods in the rehabilitation of the hemiplegic upper limb in stroke patients [26]. The largest study conducted to date involved 376 patients and demonstrated a positive effect of VR-based rehabilitation [27]. Moreover, recent literature reviews [28] have provided evidence for improvement in upper limb motor function and daily life activity after VR-based training compared with standard interventions. However, clinical evidence based on rigorous RCTs on the effect of the combined use of observation of actions followed by their immediate imitation in a VR environment (AO + VR therapy) is lacking, especially in the case of rehabilitation applied during the chronic phase after a stroke.

The main hypothesis of the study is that, for the recovery of motor function of hemiplegic stroke patients in the chronic phase, a combined rehabilitation treatment (AO + VR therapy) is more effective than a control treatment (control observation – CO) based on the observation of videos without motor content (e.g., environmental natural scenes), followed by the execution of actions in VR (CO + VR control therapy).

In sum, the planned trial will examine the following hypotheses:

AO + VR is an effective tool for promoting upper limb control in paretic stroke patients, and its effects are greater than CO + VR control treatment.Motor performance, cognitive level, and structural brain damage assessed before treatment are correlated to the degree of improvement resulting from the AO + VR intervention.The AO + VR intervention results in greater plastic functional changes of the MNS activity compared with the effects of the CO + VR control treatment.

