### Exclusion criteria

a) Presence of severe cognitive impairment (score < 20 at Mini Mental State Examination [MMSE]).b) Presence of severe forms of unilateral spatial neglect, controlled using the Bells Test (cut-off = / > 50%) [29].c) Presence of severe ideomotor Apraxia [30].d) Presence of severe anosognosia, assessed by clinical examination.e) Presence of severe language comprehension deficits, assessed by clinical examination.f) Presence of severe untreated psychiatric disorders.g) Sensory impairments hindering participation and/or not compensated visual deficits of central origin.h) Drug-resistant epilepsy.

A subgroup of patients will be selected to perform a magnetic resonance imaging (MRI) assessment. For these participants (approximately 10 for each group), additional exclusion criteria will be:a) Insufficient cooperation to perform neuroimaging studies lasting approximately 45 min.b) Presence of exclusions for 3 T MRI investigations (such as metal implants, prostheses, shunts, etc.). These exclusions will be controlled using an ad hoc questionnaire.

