### Statistical analyses

#### Analysis of primary and secondary outcomes measures

Clinical data will be managed and analyzed using the Statistical Package for Social Sciences (SPSS version 21.0). Descriptive statistics will include standard median, deviation, and interquartile distance calculated for both experimental and control groups. For the evaluation of the primary endpoint, the t-Student test for independent samples will be used. In case of excessive deviation from normality, similar non-parametric test (Mann Whitney) will be used.

The primary analysis will be carried out on all participants enrolled in the study, according to the *intention-to-treat* principle. Changes in motor performance between T0 and the subsequent longitudinal evaluations (T1, T2) will be assessed using the repeated measures Analysis of Variance (rmANOVA) with a mixed design 2 × 3, considering the group as “between subjects” factor and the time point measure (T0, T1, T2) as “within subjects” factor.

Missing data will be treated implementing a linear mixed model (LMM) on a “long” database, avoiding “listwise deletion” (elimination of all information related to the subject with missing data). The estimation of parameters deriving from the mixed model will be compared with that related to the rmANOVA analysis, also to assess the impact of missing data. The analyses related to the secondary endpoints will be carried out by applying the same LMM model. Statistical significance will be set at two-tailed alpha error values of *P* < 0.05.

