Concerning the role of MNS plastic reorganization in improving motor learning, lesion localization could represent a limiting factor when the lesion affects the cortical areas associated with MNS activity. Nonetheless, a large network of cortical and subcortical areas may provide multiple compensation mechanisms, facilitating motor re-learning in hemiplegic chronic patients. Thus, imaging studies are crucial to explore the potential of the MNS for rehabilitation and to determine which patients may benefit from specific types of AOT treatments. The fMRI assessment included in this protocol specifically aims to investigate the possible functional changes in the MNS activity of patients treated with AO + VR intervention compared to those treated with the control intervention. In particular, this investigation may allow a direct comparison of the patient’s brain activation during the observation and execution of goal-directed actions, enabling the study, for example, of the lateralization of neural activation and the extension of the activated clusters within the MSN. Also, the degree and lateralization of activation in the ipsilesional/contralesional hemisphere may correlate with improvements in arm/hand motor function parameters assessed through the primary and secondary motor outcome measures. This analysis will make it possible to identify the clinical features of stroke patients who would benefit most from AO + VR treatment, thus strengthening the evidence of its effectiveness in specific patients.

The integrated approach described in the present protocol requires a multi-professional team, to plan well-designed randomized controlled trials with the possibility of correlating measures of functional outcomes, neuropsychological assessment, and biological parameters obtained using brain imaging techniques.

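### Hypothesis 2 and the Discussion's who-benefits sentence rest on correlations with no stated between-arm contrast, so they cannot separate prognosis from response to action observation

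*Protocol article*

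**What the plan says.** The Background section lists three hypotheses. The first compares the arms: "its effects are greater than CO + VR control treatment". So does the third, on plastic changes in mirror-neuron activity: "compared with the effects of the CO + VR control treatment". The second states that pre-treatment motor performance, cognitive level and structural brain damage "assessed before treatment are correlated to the degree of improvement resulting from the AO + VR intervention", and names no comparator.

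The Discussion says that the degree and lateralization of activation "may correlate with improvements in arm/hand motor function parameters assessed through the primary and secondary motor outcome measures". It continues: "This analysis will make it possible to identify the clinical features of stroke patients who would benefit most from AO + VR treatment".

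The section on analysis of primary and secondary outcomes gives an independent-samples t-test for the primary endpoint, then a 2 × 3 repeated-measures ANOVA with group "as “between subjects” factor and the time point measure (T0, T1, T2) as “within subjects” factor", and a linear mixed model for missing data and secondary endpoints. Neither that section nor the fMRI analysis section contains a term for a baseline feature or its interaction with arm.

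The MRI subgroup is small: "For these participants (approximately 10 for each group". It is the only source of structural imaging that the article describes.

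**The concern.** Saying who benefits most from AO + VR is a claim about effect modification: the difference between AO + VR and CO + VR depends on the feature. A correlation between a feature and improvement among treated patients does not measure that. Improvement from T0 to T1 under AO + VR also contains the effect of the VR exercises, which the control section says are of the same type in both arms. It further contains the effect of usual rehabilitation, which continues, and any recovery, practice effect or regression to the mean.

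Baseline motor level is a particular problem. The experimental treatment section ties the exercise set to baseline hand ability, and controls do the same type of exercises. Motor level may therefore predict improvement in both arms through training content alone.

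At stake is that ordinary prognostic features are reported as markers of response to action observation, although the trial will hold the CO + VR data needed to check this.

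**Working it through.** **Inputs from the article.** Difference 7 BBT points, SD 11.3, power 80%, drop-out 10%, 47 per group (Sample size); two-sided alpha 0.05 (Statistical analyses); 1:1 allocation (Randomization); about 10 MRI patients per arm (Functional MRI study). The article gives no correlations, so all those below are assumptions.

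**Step 1: the plan's own figure.** Normal approximation: n = 2(1.960 + 0.842)² × 11.3² / 7² = 40.9, so 41 per arm. The t-based calculation gives 41.9, so 42 per arm, and 42 / 0.9 = 46.7, so 47. The stated size reproduces and is not in dispute. I take 42 completers per arm below.

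**Step 2: a purely prognostic feature.** Feature and improvement were simulated as standard normal with the same correlation r in both arms, so there is no differential benefit (20,000 runs). Two tests were compared: the correlation within AO + VR, and the interaction t = (b_E − b_C) / √[s²(1/Sxx_E + 1/Sxx_C)] on 2m − 4 degrees of freedom, where m is the number per arm and b_E and b_C are the slopes in AO + VR and CO + VR.

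| Per arm | r in both arms | AO + VR correlation significant | Interaction significant |
|---|---|---|---|
| 42 | 0.3 | 50% | 5% |
| 42 | 0.4 | 77% | 5% |
| 42 | 0.5 | 93% | 5% |
| 10 | 0.3 | 13% | 5% |
| 10 | 0.4 | 21% | 5% |
| 10 | 0.5 | 32% | 5% |

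**Step 3: a feature that does modify the effect** (r in AO + VR, 0 in CO + VR).

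| Per arm | r = 0.4 versus 0 | r = 0.5 versus 0 |
|---|---|---|
| 42 | interaction power 46% | 65% |
| 10 | 12% | 17% |

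The AO + VR correlation is significant about as often here (77% and 93% at 42 per arm) as in Step 2. By itself it cannot tell the two situations apart.

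**Step 4: a conditional addition.** If baseline BBT were correlated with BBT change, then with equal variances and T0–T1 correlation r, corr(X0, X1 − X0) = −√((1 − r)/2):

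- r = 0.7: −0.39
- r = 0.8: −0.32
- r = 0.9: −0.22

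The critical |r| at n = 42 is 0.304. By Fisher's z, the chance of significance is about 72%, 53% and 29% respectively.

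**Step 5: about 10 patients.** In one arm, |r| must exceed 0.632 to be significant. For 80% power it must be about tanh(2.80/√7) = 0.785.

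**The case against.** The strongest reply is that the article never specifies an analysis confined to the AO + VR arm. A reader might infer one, because hypotheses 1 and 3 name the control and hypothesis 2 does not. But hypothesis 2 names no test and no restriction, and improvement resulting from the intervention could be read as its effect against control. An article also commonly leaves the model for a subsidiary hypothesis to the full plan. This stands: the missing interaction term is not in itself a fault, and the point concerns only what the printed wording can support.

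A reader might also take the Discussion sentence to be the conclusion drawn from hypothesis 2. The documents do not support that. The sentence follows the correlation of fMRI activation with motor improvement, and the same paragraph describes the fMRI assessment as comparing AO + VR with control. That comparison, however, concerns change in activation between groups. The correlation itself is described without a contrast between arms, so the inference to who benefits fails there too.

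Third, it is tempting to say that baseline BBT is likely to emerge as a spurious predictor. The article speaks of motor performance, not of baseline BBT against BBT change, and at a T0–T1 correlation of 0.9 the built-in value of −0.22 falls below the significance threshold. Step 4 is therefore a conditional warning.

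Finally, the primary test is an unadjusted t-test. There is no baseline-adjusted primary model to which an interaction could be added, so the remedy needs a separate model.

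**Conclusion.** The concern holds in limited form. As worded, neither hypothesis 2 nor the Discussion's activation correlation includes a between-arm contrast, so neither supports a statement about who benefits most from AO + VR. Under assumed correlations of 0.3 to 0.5 and 42 completers per arm, a feature with no differential benefit would give a significant AO + VR correlation in about 50% to 93% of trials, against about 5% for the interaction test. These percentages illustrate the mechanism; they are not estimates for this trial.

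If a full analysis plan defines an interaction, the analysis would be sound, but the hypothesis and the Discussion would still need to be worded to match it. The primary endpoint, its test and the sample size are untouched. This should be corrected, but it does not threaten the main result.

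**What to change.** 1. Restate hypothesis 2 as exploratory: whether the AO + VR versus CO + VR difference varies with baseline features, tested as feature × arm interactions using both arms.
2. Fit these in a separate model of T1 BBT adjusted for baseline BBT, or as a feature × group × time term in the planned mixed model. Cover baseline motor level (for example the hand-use stratum already used in randomization) and MMSE. Report interaction estimates with confidence intervals.
3. Label associations with structural damage and fMRI activation, at about 10 patients per arm, as descriptive.
4. Limit the Discussion sentence to prognostic or exploratory association.

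This needs one additional model and some rewording, with no extra patients or assessments, since both arms are measured anyway. The article states that recruitment had not begun at submission. The downside is the limited interaction power shown in Step 3: a non-significant interaction would not show that benefit is uniform, and the claim becomes more modest.

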## Methods/Design

### Study design

This study will consist in a multicentric randomized allocation concealed (waitlist-controlled) and evaluator-blinded clinical trial (RCT) with two investigative arms, using an intensive rehabilitation program based on AO followed by imitation in VR (AO + VR) (experimental intervention) compared with a control treatment based on observation of control videos (CO) followed by action execution in VR (CO + VR) (control intervention) (see Fig. 1 for a visualization of the flow diagram of the RCT in accord with CONSORT guidelines). This study protocol is in line with the recommendations for clinical trials (SPIRIT) guidelines (Additional file 1).

**Fig. 1 Fig1:**
[figure not shown]
Flow diagram of AOT based on VR study according to CONSORT guidelines. Abbreviations: BBT = Box and Block Test; AO + VR = experimental intervention based on action observation therapy based on virtual reality techniques; CO + VR = control intervention based on observation of control videos followed by the execution of actions using virtual reality

### Participants

In general, eligible patients will be adults with a clinical diagnosis of stroke (from 3 to 18 months after the acute event, controlled via medical history and patient’s data in the respective rehabilitation center), resulting in primarily motor symptoms with unilateral upper limb paresis and residual movement ability. Only patients with severe motor symptoms or further severe neuropsychological deficits will not be eligible to participate. The multicentric study will take place in two clinical centers representing the main Italian venues for stroke rehabilitation based on VR, i.e., the “Cardinal Ferrari Center” (S. Stefano Riabilitazione) (Parma, IT) and the “Clinical Institute Quarenghi” (Bergamo, IT).

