### Concomitant care

Participants will continue to take medications for other conditions and rehabilitation treatments as usual care.

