### Assignment of intervention

#### Randomization

Participants will be randomly assigned to either control or experimental group with a 1:1 allocation using a computer-generated randomization schedule, stratified by clinical level of the hand use (minimal vs. discrete). In particular, permuted blocks of random sizes will be used. The block sizes will not be disclosed, to ensure concealment. All randomization, sequence generation, and preparation of group allocation materials will be performed by an independent researcher, who has no direct contact with the clinical aspects of the trial.

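### The main hypothesis is framed for the chronic phase, but the trial enrols patients 3 to 18 months after stroke, leaves chronic undefined, and has no term for time since stroke in its stated analyses

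*Protocol article*

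**What the plan says.** **Target population.** In the Background, the main hypothesis is stated "for the recovery of motor function of hemiplegic stroke patients in the chronic phase". The gap in evidence that motivates the trial is said to be marked "especially in the case of rehabilitation applied during the chronic phase after a stroke". The Discussion returns to the same group when it speaks of mechanisms "facilitating motor re-learning in hemiplegic chronic patients".

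**Enrolled population.** The Participants section admits adults "from 3 to 18 months after the acute event", verified from the medical history and centre records. The inclusion and exclusion criteria do not narrow this window, and no section says when the chronic phase begins.

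**Randomisation.** The only stratification factor is level of hand use, minimal or discrete.

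**Analysis.** The section on primary and secondary outcomes fixes the main test: "For the evaluation of the primary endpoint, the t-Student test for independent samples will be used". Mann-Whitney is the fallback. The longitudinal analysis is a 2 × 3 repeated measures ANOVA with group and time point only. A linear mixed model (LMM) handles missing data and the secondary endpoints, and no covariates are named for it. Time since stroke is also absent from the baseline correlates of improvement in the second numbered hypothesis.

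**Background care.** Participants in both arms continue medication and "rehabilitation treatments as usual care".

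**The concern.** The article frames its question for one population and recruits from a window that it never equates with that population. If chronic begins at any point later than 3 months, the sample mixes patients on both sides of the boundary, and the single between-arm contrast averages over them. Reported under the stated hypothesis, that average would read as a chronic-phase effect, although nothing in the plan shows that it is one. If chronic is meant to begin at 3 months, the article should say so. Either way the text needs a change.

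The second issue is precision. The window spans a six-fold range (18/3). If outcome varies with time since stroke, an unadjusted test leaves that variation in the error term, and stratifying by hand use does not control chance differences between arms in time since stroke. The variable is already held for every patient, so leaving it out saves nothing.

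**Working it through.** **1. The plan's own figure.** Inputs from the Sample size section: difference 7, SD 11.3, power 80%, drop-out 10%. From the analysis section: two-sided alpha 0.05.

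- Normal approximation: n = 2(1.96 + 0.8416)² × 11.3² / 7² = 40.9, so 41 per arm. 41/0.9 = 45.6, so 46.
- Noncentral t: 42 per arm gives power 80.1%. 42/0.9 = 46.7, so 47.

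The stated 47 per group (94 in total) is reproduced. It concerns all enrolled patients, and this point does not disturb it.

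**2. Does the text tie the window to the chronic phase?** The main hypothesis, the evidence gap and one passage of the Discussion say chronic. Eligibility says 3 to 18 months. No definition links them. Any boundary above 3 months yields a mixed sample. The documents give neither a boundary nor the share of patients on each side.

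**3. What a covariate could recover.** Let r be the correlation of time since stroke with BBT at T1 (assumed). Residual SD = 11.3 × √(1 − r²). With 42 evaluable per arm, power ≈ Φ(7 / (SD × √(2/42)) − 1.96).

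| r (assumed) | Residual SD | Power |
|---|---|---|
| 0 (unadjusted) | 11.30 | 81.0% |
| 0.1 | 11.24 | 81.4% |
| 0.3 | 10.78 | 84.5% |
| 0.5 | 9.79 | 90.6% |

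The unadjusted row is 81.0% rather than 80.1% because this table uses the normal approximation. If baseline BBT is also in the model, the relevant r is the partial correlation given baseline, which may be smaller.

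**4. Chance imbalance.** With 47 per arm and an early share f (assumed), the share can differ between arms by up to 1.96 × √(2f(1 − f)/47):

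- f = 20%: 16 percentage points.
- f = 50%: 20 percentage points.

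With an assumed 5-point prognostic gap between early and late patients, the BBT contrast would shift by 5 × 0.16 = 0.8 to 5 × 0.20 = 1.0 points, against a 7-point target.

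**5. Could the trial separate early from late effects?** For a two-way split, the 95% half-width of the difference between the two treatment effects is 1.96 × 11.3 × √(2/n_early + 2/n_late), with n per arm out of 42 evaluable.

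- Early share 20% (8 and 34): 22.15 × √(0.250 + 0.059) = 12.3 blocks.
- Early share 40% (17 and 25): 22.15 × √(0.118 + 0.080) = 9.8 blocks.

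These depend on the assumed shares, not on where the boundary lies. Both exceed the 7-block target effect.

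**The case against.** The case against is substantial, and much of it stands.

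- **The boundary is not in the documents.** A 6-month cut-off, or the statement that patients are still recovering at 3 months, would have to be brought in from outside. The authors may simply regard 3 to 18 months as chronic. This stands. It limits the point to an undefined term that must be reconciled with the window.
- **The chronic wording is not uniform.** The first numbered hypothesis, the Abstract's statement of purpose and the opening of the Discussion refer to stroke patients without naming a phase. This also stands, and it makes the rewording small. It does not remove the mismatch, because the main hypothesis and the rationale do name the chronic phase.
- **There is no bias.** Allocation is 1:1 against a concurrent control with the same number of sessions. Natural recovery and usual care act on both arms, including between T1 and T2. A reader might infer that spontaneous recovery confounds the treatment or retention comparison. The design does not support that.
- **The trial is not shown to be underpowered.** A reader might compute power in a later subgroup alone and conclude that the main hypothesis is underpowered. The plan runs no such test, and that calculation needs both a boundary and a share that the documents lack. If the effect is similar across the window, power stays at the planned 80%. Nothing in the documents indicates that it differs.
- **The planning SD of 11.3 may already include variation due to time since stroke.** That is possible. Adjustment would then be a gain over the plan rather than repair of a shortfall.
- **Covariates are commonly left to the analysis plan.** That is fair for the LMM. It does not cover the primary test, which the article fixes as a t-test or Mann-Whitney, neither of which takes a covariate.
- **One stratification factor is a defensible choice for 94 patients.** Agreed; no change to stratification is needed.

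**Conclusion.** The point holds as a mismatch between the stated question and the enrolled population, together with a missed and almost free gain in precision. It is not a flaw in validity: the between-arm test is unbiased in expectation, and 47 per group is correct for the population enrolled.

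The interpretive cost has no numerical size, because the documents give neither a definition of chronic nor the mix of patients. The precision cost ranges from negligible (81.0% to 81.4% power at r = 0.1) to appreciable (90.6% at r = 0.5). These correlations are assumptions, and the gain may be smaller once baseline BBT is in the model.

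It might be inferred that the trial should report, or be powered for, a separate chronic-phase effect. With half-widths of about ±10 to ±12 blocks for an early/late contrast, under assumed early shares of 40% and 20%, it could not separate the phases even if they differed by the full 7-block target.

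**What to change.** 1. **Wording.** State the main hypothesis, and later the conclusion, for stroke patients 3 to 18 months after the event. Alternatively, define chronic explicitly so that it matches the eligibility window. Use the same term in the rationale and the Discussion. Eligibility does not change.
2. **Model.** Prespecify continuous time since stroke at T0 as a covariate in the primary BBT analysis, for example an ANCOVA at T1, or an LMM over the time points, that also includes baseline BBT and the hand-use stratum. Name this as the primary analysis in place of the unadjusted t-test, so that there are not two competing primary results.
3. **Exploratory estimate.** If the treatment effect is examined by time since stroke, label it exploratory, give it with its confidence interval, and do not present it as a powered test of a chronic-phase effect.

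**Cost.** Changes to a few sentences in the hypothesis and analysis sections. No new measurements or patients are needed, because time since stroke is already verified for everyone and N = 94 does not have to rise. The Study Status section says recruitment had not begun at submission, so the change could still be prespecified at that point. The trade-off is that the headline claim is tied to the 3-to-18-month population, not to the chronic phase as such.
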